## Description of protocol

### Aims

The primary aim of the present study is to explore whether the 16 weeks therapy model with clomiphene citrate (CC) leads to stimulation of endogenous luteinizing hormone (LH) and testosterone production, if the treatment model is safe, and if the model is more effective in reducing AAS withdrawal symptoms compared to no intervention. The secondary aims are to detect health risks during ongoing AAS use in the intervention group only and assess whether and to what extent the health risks are reduced 12 months after cessation of AAS.

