**Inclusion criteria**		
Age	≥18 years	≥18 years
AAS use	Continuous AAS use ≥6months	Cycle, ≥6weeks between cycles
Dose	Supraphysiological	≥400 mg/week
AAS dependence	3 or more items last 12 months: tolerance, withdrawal, increased amount, unsuccessful efforts to reduce or cease use, ↑time to obtain/use substances, ↓social/recreational/occupational activities due to use, continued AAS use despite mental and/or physical side effects	No
Plan to cease AAS use	Wish to cease use, previous unsuccessful attempts	No
SUD treatment	Being enrolled in or referred to Substance Use Disorder (SUD) treatment	No
Hormonal and liver status at intervention start	Serum testosterone < 25 nmol/l, liver enzymes alanine transaminase (ALT) and aspartate transaminase (AST) < 3 x upper limit of normal range (ULN) (normal range ALT 10–70 U/L, AST 15–45 U/L)	No

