#### Self-reported mental health, well-being and AAS withdrawal symptoms

To investigate mental health state, wellbeing and AAS-withdrawal symptoms after AAS cessation, the following self-reporting questionnaires will be administered via a web-app every second week for 16 weeks for both groups and at follow-up at 6 and 12 months for the intervention group: Hopkins Symptom Checklist-10 (HSCL-10) to evaluate psychological distress, suicidal ideation item from Montgomery and Åsberg Rating Scale (MADRS), items from Health-related quality of life (HRQOL) to evaluate sexual function, Shortened Fatigue Questionnaire, WHO-5 Wellbeing Index and Jenkins Sleep Scale (JSS), Body Perception Questionnaire; and Visual Analog Scale (VAS) to measure aggression, cognitive function, body image and pain. Treatment satisfaction will be assessed using VAS for the intervention group only.

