### Data analysis plan

Data analyses will follow a full analysis set, with a per protocol plan. Descriptive statistics will be used when appropriate and for reported adverse events. For between-group comparisons and to control for the effect of baseline characteristics, we plan to use General Linear Mixed Models (GLMM) with a within subject repeated measures design at baseline, 6 months and 12 months. In cases where the outcomes do not meet the normality assumption, we will apply a General Alinear Mixed Models (GAMM) approach. The results of statistical analyses will be performed using 95 % CIs, and a two-sided P value of < 0.05 will be used to indicate statistical significance. General linear models may be utilized in cases where GLMM/GAMM is considered inappropriate. Two sample *t*-tests will be used for between-group comparisons of numerical variables, when we see no need to adjust for confounding variables. Numerical data not following normal distribution will be presented as medians (25th-75th percentiles), using non-parametric tests such as the Wilcoxon rank sum tests (Mann-Whitney) to compare differences between groups. Chi^2^-tests and Fischer's exact will be applied for categorical variables. Per protocol analysis will be applied in cases of missing data to detect any discrepancy that might affect the robustness of the results. All statistical calculations and analyses will be conducted using up-to-date versions of the statistical software STATA and SPSS.

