### Scientific rationale for study design

The chosen design served three primary purposes (a) to assess the feasibility and acceptability of the intervention, (b) to evaluate its safety, and (c) to examine its effect on symptoms and objective measures of hypogonadism. The cohort design for the intervention group allowed for investigating potential health risks reduction following cessation of AAS use. Although a randomized controlled trial (RCT) is considered the gold standard methodology, conducting a preliminary test of the intervention before proceeding to an RCT is essential. Additionally, this approach facilitates the determination of effect sizes for use in sample size calculations for future RCTs [29]. However, it is acknowledged that the comparison group may differ from the intervention group on certain variables, as they may not share the same intention to permanently cease AAS use.

The study exclusively recruits male participants as we investigate the effect of treatment of androgen deficiency due to AAS induced male hypogonadism. The primary endpoints (symptoms of hypogonadism such as depression, anxiety, fatigue, reduced libido, and erectile dysfunction, and other symptoms related to AAS use) were developed in collaboration with a user panel comprising people with prior AAS experience and clinicians from the outpatient SUD clinic with experience of providing treatment to the patient group. These endpoints are considered reliable clinical indicators of the intended intervention effect.

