## Limitations

This non-randomized proof-of-concept intervention study with a small number of participants, is the first study to test off-label use of CC with the intention to restart endogenous testosterone production upon cessation of AAS use among men with AAS induced hypogonadism. The study will compare symptoms of AAS induced hypogonadism and other AAS-related side effects between the group receiving CC and a group of male AAS users not receiving the intervention. The comparison group differs from the intervention group as the participants may have less serious AAS use and less symptom burden during use as they mostly use AAS as cycles with an intention to cease use only temporarily. Moreover, the 12 months follow-up on examination of health risks in the intervention group may be too short as sperm quality is found to take up to 3 years to recover [15] and men with former AAS use is found to have lower plasma testosterone levels and more symptoms suggestive of hypogonadism than healthy controls several years after AAS cessation [30]. Finally, many health risks are associated with AAS use [[4], [5], [6]], and measures of a selection of health risks are included in this study. However, detailed, and frequent monitoring using objective biological measures is a strength and the study may provide valuable clinical insights, enabling the exploration of whether adjustments are needed for the intervention. Furthermore, the results may be used to determine the sample size and informing the design of future RCT or case comparison studies.

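### Beside its adjusted mixed model, the plan allows unadjusted tests at discretion between non-randomised groups that differ by entry rule, and the adjusted model's time points miss the data both groups share

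*Protocol article*

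**What the plan says.** The Data analysis plan first gives an adjusted method: "For between-group comparisons and to control for the effect of baseline characteristics, we plan to use General Linear Mixed Models (GLMM". It places this model "with a within subject repeated measures design at baseline, 6 months and 12 months". Further on it adds that two-sample t-tests "will be used for between-group comparisons of numerical variables, when we see no need to adjust for confounding variables". It does not say who judges the need, when, or by what criterion. The rank-sum, chi-square and Fisher tests that follow are unadjusted too.

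Allocation is not randomised. Table 1 gives the two groups different entry rules:

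- **Use pattern:** continuous for at least 6 months, against cycles with breaks of at least 6 weeks.
- **Dependence:** at least 3 criteria, against no such requirement.
- **Intent:** a wish to stop after failed attempts, against no such requirement.
- **Care:** "Being enrolled in or referred to Substance Use Disorder (SUD) treatment", against no such requirement.

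Study design adds permanent against temporary cessation. The Limitations say of the comparison group that "the participants may have less serious AAS use and less symptom burden during use".

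One part of the primary aim is to explore "if the model is more effective in reducing AAS withdrawal symptoms compared to no intervention". Outcomes and instruments lists change in self-reported symptoms, assessed in both groups, as a primary outcome. The Scientific rationale says "this approach facilitates the determination of effect sizes for use in sample size calculations for future RCTs". The Specifications table and the Limitations repeat the sample-size use in softer terms.

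**The concern.** A design that expects the groups to start at different symptom levels cannot leave it to judgement whether that difference matters. If the test is unadjusted, the between-group difference mixes starting severity with treatment. If the choice is made after the data are seen, it can follow the result.

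Two uses are at stake. One is the answer to the comparative part of the primary aim. The other is the effect size that may be carried into a later RCT, where a bias of a few tenths of an SD changes the sample size several-fold.

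**Working it through.** **1. Which time points the groups share.** The section on self-reported symptoms says the questionnaires are given "every second week for 16 weeks for both groups and at follow-up at 6 and 12 months for the intervention group". The adjusted model is set at baseline, 6 and 12 months. The two schedules have only baseline in common, so the stated adjusted model contains no follow-up visit at which both groups have data. The two-weekly scores to week 16, where both do, have no stated adjusted model.

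**2. Whether the baseline score is available.** Study design says participants of both studies report symptoms during ongoing use and after cessation. The covariate therefore exists in both groups.

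**3. How large the bias could be.** The plan gives no figure on this point, so this is an illustration.

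- From the plan: total sample 52, so 52/2 = 26 per group; two-sided 5% level. Whether 52 follows from the plan's own effect size is a separate question and is not used here.
- Assumed: true effect zero; equal SDs of 1; correlation r of 0.5 or 0.7 between baseline and follow-up; intervention men start worse by b = 0.5 or 0.8 SD; men with the same baseline score have the same expected follow-up score in either group.

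Formulas, with higher scores meaning worse symptoms, intervention minus comparison:

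- Follow-up score: bias = r·b, against treatment.
- Change score: raw bias = (r − 1)·b, towards treatment. The SD of change is √(2(1 − r)), so the standardised size is b·√((1 − r)/2).
- Rejection rate: two-sided t-test, 50 degrees of freedom, non-centrality d·√(26/2).

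| b | r | Follow-up score: d against treatment | Rejections | Change score: d towards treatment | Rejections |
|---|---|---|---|---|---|
| 0.5 | 0.5 | 0.25 | 14.3% | 0.25 | 14.3% |
| 0.5 | 0.7 | 0.35 | 23.6% | 0.19 | 10.5% |
| 0.8 | 0.5 | 0.40 | 29.3% | 0.40 | 29.3% |
| 0.8 | 0.7 | 0.56 | 50.8% | 0.31 | 19.5% |

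The nominal rate is 5%. Nearly all rejections fall in the tail named in the column; the other tail holds at most about 0.4 percentage points.

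**4. Sensitivity to the last assumption.** Under it, adjustment for the baseline score is unbiased. If instead the gap between the groups stayed constant without treatment, the change score would be unbiased, the follow-up score biased by b, and the baseline-adjusted estimate biased by (1 − r)·b: from 0.3 × 0.5 = 0.15 to 0.5 × 0.8 = 0.40 SD against treatment. The documents do not show which holds, so both analyses need to be seen.

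**5. Consequence for a later RCT.** Take a true d of 0.4, which needs 99 per arm for 80% power (normal approximation).

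- If bias makes it look like 0.6, the RCT gets 44 per arm and has 47% power.
- If it looks like 0.2, the RCT gets 393 per arm.
- Without any bias, the 95% CI half-width for d = 0.4 at 26 per group is 1.96·√(2/26 + 0.4²/104) = 0.55.

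**The case against.** The strongest reply is that the adjusted mixed model comes first and the t-test is only a conditional addition. That is correct. A reader might infer that t-tests are the planned efficacy analysis, and the text does not support this. The sentence speaks of numerical variables in general and could cover group descriptions. Nothing says that a t-test result will answer the primary aim or supply the RCT effect size. What stands is that the sentence does not exclude symptom outcomes, and that the adjusted model as timed cannot serve the shared follow-up.

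A reader might also infer that unadjusted tests would produce false evidence of benefit in up to half of such studies. That does not follow. The 51% belongs to the follow-up-score test and lies almost wholly on the side of harm if intervention men start worse. The primary outcome is change, where the assumed range gives about 11-29%.

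The authors are open about the weakness. The aim is to explore, the study is called proof-of-concept, non-equivalence is conceded twice, and two of the three statements on sizing are permissive. The therapy model openly includes gel and optional hCG, so only SUD care lies outside it. This lowers the severity. It does not remove the conflict between an admitted baseline difference and a licence to ignore it.

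A list of confounders is commonly left to the analysis plan, and its absence is not held against this article. The point is a rule that the article does state.

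**Conclusion.** The point holds in a limited form. The main between-group method is adjusted, but the article also allows unadjusted tests without a criterion, between groups that differ by entry rule and probably in starting symptoms. It gives no adjusted model for the visits at which both groups have data.

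Under the stated assumptions the bias is a standardised 0.19-0.40 towards treatment on change scores and 0.25-0.56 against it on follow-up scores. The 0.5-0.8 SD gap and the correlation of 0.5-0.7 are assumptions without a source in the document. The Limitations support the direction of the gap only, not its size.

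One might conclude that mandatory adjustment would make the contrast a valid estimate of effectiveness. It would not. Dependence, use pattern, intent and SUD care nearly coincide with group, so there is little overlap on which to adjust. The contrast therefore remains exploratory and should not supply the effect size for an RCT.

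**What to change.** 1. In the Data analysis plan, remove the unadjusted option for between-group symptom outcomes. It may stay for describing baseline characteristics.
2. For the shared two-weekly data to week 16, state one adjusted model. It always includes the ongoing-use baseline score of the same scale, and the change-score result is shown beside it. Keep the 6- and 12-month model for within-group change in the intervention group.
3. Say that this adjustment does not remove confounding by dependence, use pattern, intent or SUD care.
4. In the Aims, word the comparison as exploratory and descriptive of the whole package: clomiphene, gel, optional hCG and SUD care.
5. In the Specifications table, Scientific rationale and Limitations, say that the between-group effect size will not be used to size an RCT. Carry forward SDs, correlations, attrition and adherence, with confidence intervals.

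The cost is wording and slightly more analysis. No new visits, data or participants are needed. The downside is a weaker stated claim.

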## Background

Non-prescribed AAS are predominantly utilized by male recreational athletes in cyclic patterns, with intermittent breaks or continuous administration. Global lifetime prevalence of AAS use among men is estimated to be 6.4 %, but is found higher in subpopulations [1] and associated health risks and behavioral outcomes make AAS use a public health concern [2]. The wide range of adverse effects on mental [3] and physical health [[4], [5], [6]] includes negative effects on the cardiovascular system such as ventricular dysfunction [7], myocardial hypertrophy [8], hypertension [9], severe biventricular cardiomyopathy [10], acute myocardial infarction and sudden cardiac death [8,11]. Increased carotid intima-media thickness, reduced arterial elasticity and lower carotid artery compliance are early predictors of atherosclerosis and cardiovascular risk that are found among men with long term AAS use [12]. AAS use is also associated with altered renal, hepatic and metabolic functions [13]. High androgen levels might lead to gynecomastia and several dermatological conditions, and infertility during ongoing use is common due to the disruption of hypothalamic-pituitary-gonadal (HPG) axis [14,15].

One in three people using AAS seem to develop a dependence syndrome characterized by a pattern of escalating doses and reduced breaks between cycles, or continuous use despite experiencing adverse effects and a desire to cease use [16]. The neuroendocrine mechanism of AAS dependence is linked to suppression of the hypothalamic-pituitary-gonadal (HPG) axis leading to AAS-induced hypogonadism (ASIH) [14]. The features of androgen deficiency (fatigue, depression, anxiety, and sexual dysfunction) will first occur weeks after AAS cessation. The endogenous testosterone production typically recovers after 3–12 months, but this phase is hard to endure [17], often resulting in restart of AAS use.

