Despite experiencing health problems associated with AAS use, many individuals fail to receive treatment [18,19]. This reluctance to engage with health services may be attributed to limited treatment options and insufficient awareness of AAS among clinicians. Many individuals who use AAS feel stigmatized, and fear being identified with or labelled as either drug users or sport cheats, with this acting as a further barrier to service engagement [20]. Instead of seeking health services, people who use AAS commonly seek knowledge among peers including in online communities. When AAS use is ceased, some may self-initiate Post Cycle Therapy (PCT) with non-prescribed hormonal substances in various combinations and doses with the intention to restore the HPG-axis faster. As one of few countries, Norway has integrated AAS and other performance and image enhancing drugs (PIEDs) in the National Drug Policy. Possession and use of AAS and other PIEDs became criminalized in 2013, and people with current or previous AAS use got access to SUD treatment in the specialist health service. There is no consensus, nationally or internationally, on whether endocrine treatment should be used in the treatment of ASIH, but endocrinologists have proposed potential interventions [21]. There is a knowledge gap regarding treatment of this patient group, and we describe a non-randomized proof-of-concept study to test a 16 weeks off-label hormone intervention for men who struggle to cease AAS use.

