**Exclusion criteria**		
Mental health	Previous or current: Severe depression, bipolar disorder, psychosis	Reduced cognitive function (IQ<80) and/or previous or current: Severe depression, bipolar disorder, psychosis. Use of medications that may impact CNS functioning (e.g., antipsychotics, methyl phenidate, TRT)
Physical health	Hypersensitivity to clomiphene citrate, hyperprolactinemia, untreated thyroid or adrenal disease, hemoglobin >18.0 g/dl, current/previous thromboembolic disease, cardiovascular disease (arrhythmia, ischemic heart conditions, heart failure)	Traumatic brain injury with consciousness >1 min, or neurological disorders (e.g., multiple sclerosis, ischemia) or severe somatic disorders (e.g. cancer)
Substance use	No illicit substance use during intervention, <8 alcohol units/week	Problematic use of alcohol or illegal substances (evaluated with Alcohol Use Disorders Identification Test and Drug Use Disorders Identification Test C)

Recruitment for the intervention group**:** The National Steroid Project at Oslo University Hospital (OUH) will recruit participants for the intervention study through a national information service [24], the outpatient SUD clinic at OUH, flyers in various gyms and through advertisements on social media; Facebook, Instagram, TikTok, Snapchat and AAS user forum.

Recruitment for the comparison group**:** Advertisements on social media.

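### Per-protocol analysis is named as the robustness check for missing data, which it cannot perform, and a condition knowable only during treatment is listed as an exclusion criterion for the intervention group alone

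*Protocol article*

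**What the plan says.** Under Data analysis plan, the protocol article opens with "Data analyses will follow a full analysis set, with a per protocol plan". It does not say which set carries the main result. It plans mixed models for repeated measures at baseline, 6 and 12 months, and allows two-sample t-tests and rank tests in some cases. The one sentence on missing data is "Per protocol analysis will be applied in cases of missing data to detect any discrepancy that might affect the robustness of the results".

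Table 1, in the exclusion rows for the intervention group, lists "No illicit substance use during intervention, <8 alcohol units/week". The comparison column instead excludes problematic alcohol or drug use, judged by screening questionnaires, and sets no condition on behaviour during the study.

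On the likelihood of relapse, the Background says of the recovery period after cessation: "but this phase is hard to endure [17], often resulting in restart of AAS use". The inclusion criteria require earlier failed attempts to stop. Outcomes and instruments lists AAS use and adherence to substance-use treatment among the 12-month outcomes. Urine is screened for AAS during the intervention and at follow-up (Biological assessments for the intervention group).

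**The concern.** A check on missing data should ask how far the conclusion depends on what the unseen men would have scored. A per-protocol analysis asks what the result is among men who adhered. Agreement between the two analyses would reassure readers without cause. Disagreement could reflect adherence and not missingness.

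This matters here because the protocol itself describes relapse as common and driven by symptoms. It recruits men who have failed to stop before, and it counts AAS use as an outcome. Loss is therefore unlikely to be random, and an analysis that leaves these men out conditions on something close to the outcome.

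The Table 1 entry adds a second route. A criterion that can only be assessed after enrolment cannot govern eligibility. If it were used to take men out of the analysis, it would select on behaviour after baseline in one group and not in the other. The study is meant to supply effect sizes for later randomised trials (Scientific rationale for study design), so a distorted estimate would carry forward.

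**Working it through.** **Inputs.** The protocol gives no relapse rate, dropout rate or score difference, so there is no figure of its own on this point to reproduce. From Sample size determination: 25-30 men per group, a target effect of d = 0.4, and a total of 52, taken here as 26 per group. From Data analysis plan: two-sided 5% significance, which is 2.5% in the favourable direction. Assumed: share lost r = 20-40%, and lost men scoring Δ = 0.5-1.0 SD worse than the rest.

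**Step 1: shift from leaving men out.** If retained men have mean m, the whole group has mean (1 − r)m + r(m + Δ) = m + rΔ. Analysing only the retained men moves the group mean by rΔ.

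**Step 2: false favourable findings.** Two groups of 26 with no true difference were simulated 20,000 times per setting. Lost men were dropped from the intervention group only.

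| r | Δ (SD) | Shift rΔ (SD) | Falsely significant in favour |
|---|---|---|---|
| 20% | 0.5 | 0.10 | 5.3% |
| 30% | 0.5 | 0.15 | 7.1% |
| 40% | 0.5 | 0.20 | 8.7% |
| 20% | 1.0 | 0.20 | 9.6% |
| 30% | 1.0 | 0.30 | 15.5% |
| 40% | 1.0 | 0.40 | 22.9% |

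Keeping every man with his value holds the rate at about 2.5%. Relative to d = 0.4, the shift runs from 0.10/0.4 = 25% to 0.40/0.4 = 100%. The men remaining number between 25 × 0.6 = 15 and 30 × 0.8 = 24.

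**Step 3: reversed direction.** If men who restart feel better because of the steroids, Δ is negative. With Δ = −0.4 and r = 10-50%, the shift is 0.1 × 0.4 = 0.04 to 0.5 × 0.4 = 0.20 SD against the intervention. With Δ = −0.5 to −1.0, the tabled shifts apply with opposite sign.

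**Step 4: why the stated check can miss this.** Suppose 30% have no outcome recorded, would have scored 1 SD worse, and everyone with data adhered. A t-test on observed cases and the per-protocol analysis then use the same men. Both are off by 0.3 × 1.0 = 0.30 SD, and the discrepancy between them is zero.

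**The case against.** The strongest reply is that the text is less damaging than it may look.

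- The full analysis set is named first, and the sentence on per-protocol analysis reads as a secondary comparison. A reader might infer that relapsing men are removed from the main analysis. The document does not say so. Measuring AAS use at 12 months and screening urine at follow-up suggest that such men are followed.
- A reader might treat AAS relapse as the illicit use in Table 1, since the Background notes "Possession and use of AAS and other PIEDs became criminalized in 2013". That is an inference. The protocol elsewhere lists AAS apart from other substances, and it attaches no consequence for the analysis to this criterion.
- A reader might conclude that the bias favours the intervention. For symptoms the direction is open, because restarting AAS may relieve them. Comparison men can have breaks as short as 6 weeks, so some may also restart within the 16 weeks.
- Mixed models use incomplete records and are valid under missing at random, so per-protocol analysis is not the only protection.
- Definitions of analysis sets commonly sit in a full protocol or SAP that is not shown.

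All of this stands as a limit on the point, but it does not rescue the stated check. The mixed model is written for baseline, 6 and 12 months, although symptoms are collected fortnightly to week 16. As written, a man lost before 6 months contributes only his baseline, and the scores that could make missing at random plausible are left out. The permitted t-tests and rank tests use observed cases only. Missing definitions are not the complaint: the article states a specific method for a purpose that it cannot serve.

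**Conclusion.** The point holds in a limited form. Per-protocol analysis is the wrong check on robustness to missing data, the opening sentence leaves the primary set unclear, and a during-treatment condition sits among the exclusion criteria for one group. The document does not establish that relapsing men are dropped from the main analysis or from follow-up, so the bias is a risk that the wording permits and not a planned step.

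The possible shift of 0.10-0.40 SD, in either direction for symptoms, rests wholly on an assumed loss of 20-40% and an assumed difference of 0.5-1.0 SD. The false-positive rates of 5.3-22.9% further assume that losses are dropped from the intervention group only and that those men are worse. This should be fixed; confidence is moderate.

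**What to change.** - Make the full analysis set primary for every outcome: all men who start the intervention, and all comparison men with a baseline.
- Fit the planned mixed model to all available repeated measures, including the fortnightly scores, with the same rule for relapse in both groups. Do not restrict it to observations off AAS, which would itself discard data after relapse.
- Report relapse or withdrawal as an outcome proportion with an exact confidence interval, beside the symptom results, so that scores recorded after a restart are not read alone.
- Replace per-protocol as the missing-data check with a delta-adjusted or tipping-point analysis: shift the values assumed for missing men over a stated range in either direction and report where the conclusion changes. A worst-score analysis is a simpler alternative. Keep per-protocol as supportive only.
- Reconcile Table 1 with the Data analysis plan on whether illicit use during the intervention is an eligibility criterion or a condition of conduct, and state that it does not remove men from the full analysis set.

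The cost is revised wording, one extra sensitivity analysis, and estimates that may be wider or less favourable.
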